The existence of “low ESA response” patient groups, where Hb concentrations do not increase much despite ESA administration, has become a problem in recent years. Iron deficiencies are thought to be the biggest cause of low ESA response, and other influential causes include bleeding, hematopoietic inhibition (e.g., infection, inflammation, folic acid/vitamin B12 deficiency), hematopoietic tumors, blood disorders, hypersplenism, appearance of anti-EPO antibodies, insufficient dialysis, and nutrient deficiency. However, there is no clear definition for low ESA response in the current guidelines of renal anemia treatment in Japan and in Western countries. The definition of low ESA response in the “Guidelines for the treatment of renal anemia in patients with chronic kidney disease” included only the following: “In chronic kidney disease, a patient is considered to have a low response to rHuEPO therapy when rHuEPO is used subcutaneously once a week, with 6,000 units per session (6,000 units per week), and the target Hb concentration cannot be achieved (opinion). However, achieving the target Hb

concentration is difficult at the currently available doses of rHuEPO, so it is difficult to define a low response to rHuEPO therapy at the current stage”. The current status is similar in international guidelines (KDIGO), which only state the following: “Cases where increases in Hb concentration from baseline values are not seen in the first month of ESA therapy regardless of the optimal dose in terms of body weight are classified as low ESA response (no grade),” and “Cases where doses are increased up to 50% of the necessary ESA administered dose during the period when Hb concentrations were stable two times are classified as low ESA response (no grade)”. Under such circumstances, there is a need for the formulation of evidence-based indices of low ESA response and anemia treatment policies to treat CKD patients with renal anemia and low ESA response.

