### 12.3 ERI

The following five indices are considered new candidates for the ESA response indices (ERIs) to be investigated.

- ERI-1A (index according to one time point at 12 weeks)

$$\frac{\text{DA administered dose 12 weeks after the start of treatment (}\mu\text{g)}}{\text{Hb concentration 12 weeks after the start of treatment (g/dL)} \times \text{weight 12 weeks after the start of treatment (kg)}}$$

- ERI-1B (index according to one time point at 12 weeks)

$$\frac{\text{DA administered dose 12 weeks after the start of treatment (}\mu\text{g)}}{\text{Hb concentration 12 weeks after the start of treatment (g/dL)}}$$

- ERI-2A (index that considers the cumulative administered dose up to 12 weeks and changes in Hb concentration)

$$\frac{\text{Total DA administered dose up to 12 weeks after the start of treatment } (\mu\text{g})}{\text{Amount of change} \times \text{weight at 12 weeks (kg)}}$$

- ERI-2B (index that considers the cumulative administered dose up to 12 weeks and changes in Hb concentration)

$$\frac{\text{Total DA administered dose up to 12 weeks after the start of treatment } (\mu\text{g})}{\text{Amount of change}}$$

- Change in Hb concentration (changes in Hb concentration up to 12 weeks)

$$\text{Hb concentration at 12 weeks (g/dL)} - \text{prior Hb concentration (g/dL)}$$

A similar index is created for the ERI index from the Hb concentration and darbepoetin alfa administered at 16 weeks and at 24 weeks in addition to that at 12 weeks, and the associations between these indices and event occurrence are also investigated. When the ERI index at 12 weeks favorably predicts event occurrence, then whether the ERI index composed of the values at week 10, 8, 6, 4, and 2 favorably predicted the event occurrence is confirmed in order.

New indices are further explored if no associations between these index candidates and renal function deterioration or CVD events were found.

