### 13.2.2 Efficacy analysis set

The group excluding the following patients from the safety set is defined as the efficacy analysis set.

- Those who were ineligible after registration
- Those who discontinued darbepoetin alfa administration within 12 weeks after the start of treatment
- Those who do not have a single DA administration record 12 weeks after the start of treatment
- Hb concentration measurements are not obtained at the start of treatment and at 12 weeks

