### 13.3.1 Renal function deterioration, CVD event investigation

A proportional hazards model that includes the following covariates is applied, and the factors that affect event occurrence are investigated. Covariates are added or decreased as required for the investigation of the model. Hb concentration values at each measurement time point up to 24 weeks instead of week 12 of administration are also investigated. The presence of diabetic complications, arteriosclerosis, and chronic inflammation should also be considered as stratification factors. These analyses are used to investigate the prediction equation for event occurrence from the covariates.

- Age; sex; weight; eGFR, serum albumin, hemoglobin concentration, high-sensitive CRP, NT-pro BNP, folic acid, vitamin B12, serum iron, serum ferritin, and TSAT 12 weeks after the start of treatment; the presence of diabetic complications, arteriosclerosis, chronic inflammation, malignant tumor complications, hemorrhagic lesion complications, collagen disease and rheumatic disease complications, concomitant immunosuppressant or steroid use, and other myelosuppressive factors; and the darbepoetin alfa administered dose (total administered dose, administered dose 12 weeks after the start of treatment).

Next, the cut-off values of each ERI are gradually increased from the minimum value to the maximum

value; a time-dependent ROC curve of the survival time data with censoring is created, and the AUC is compared. If the cut-off value is set from the ROC curves of each obtained ERI, then these are divided into two groups at the cut-off value, Kaplan-Meier plots are created, and the annual event occurrence rate (human-year method) and 95% confidence intervals are estimated. The cut-off values of the ERIs may also be investigated using the cross-validation method, if considered useful.

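### ERI-2A and ERI-2B divide dose by a signed Hb change, so every patient whose Hb fell ranks at the good-response end of the cut-off sweep

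*Protocol*

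**What the plan says.** Section 12.3 lists five candidate indices, one of which is "ERI-2B (index that considers the cumulative administered dose up to 12 weeks and changes in Hb concentration". For ERI-2A and ERI-2B the numerator is "Total DA administered dose up to 12 weeks after the start of treatment" in µg. The denominator is "Amount of change", multiplied by weight for ERI-2A only. The only change the section defines is its fifth candidate, "Change in Hb concentration (changes in Hb concentration up to 12 weeks", computed as Hb at 12 weeks minus prior Hb. That is a signed quantity. No floor, offset or rule is given for a change of zero or below.

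Section 13.2.2 removes patients from the efficacy analysis set when "Hb concentration measurements are not obtained at the start of treatment and at 12 weeks", but it does not remove patients whose Hb was measured and failed to rise.

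Section 13.3.1 says that "the cut-off values of each ERI are gradually increased from the minimum value to the maximum" value, builds a time-dependent ROC curve for each index and compares the AUCs. If a cut-off is set, patients are divided into two groups at it. Position on the raw scale therefore decides each patient's classification.

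Section 2 describes the patients of interest as those "where Hb concentrations do not increase much despite ESA administration".

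**The concern.** Among patients whose Hb rose, a high ERI-2 value means poor response: much dose for little gain. That ordering breaks at zero change. A very small rise gives a very large positive value, and a very small fall gives a very large negative one. A single cut-off moved along this scale puts patients with falling Hb next to the best responders, and splits near-identical patients between the two extremes.

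The misplaced patients are the ones the study was set up to identify. If low response does predict renal or cardiovascular events, ERI-2A and ERI-2B will show less of that relation than the data contain. They may then lose the AUC comparison because of their algebra rather than because cumulative dose carries no information.

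The same form is to be built at 16 and 24 weeks. It is also built at earlier weeks, to see "whether the ERI index composed of the values at week 10, 8, 6, 4, and 2 favorably predicted the event occurrence", but only if the 12-week index predicts well.

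**Working it through.** **Inputs from the protocol.** ERI-2B = D / ΔHb and ERI-2A = D / (ΔHb × weight), where D is total dose to week 12 and ΔHb is Hb at 12 weeks minus prior Hb (12.3). D is above zero because the analysis set contains only treated patients (13.2.1, 13.2.2). The protocol states no figure for the size or spread of ΔHb, so there is no plan figure to reproduce.

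**Step 1: the formula alone.** Illustrative D = 180 µg, weight 60 kg:

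| ΔHb (g/dL) | ERI-2B = 180/ΔHb | ERI-2A = ERI-2B/60 |
|---|---|---|
| +2.0 | 90 | 1.5 |
| +1.0 | 180 | 3 |
| +0.1 | 1800 | 30 |
| 0 | undefined | undefined |
| −0.1 | −1800 | −30 |
| −0.5 | −360 | −6 |
| −1.0 | −180 | −3 |

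Three things follow without any distributional assumption:
- Every faller has a negative value and every riser a positive one, so all fallers lie below all risers.
- Going from +0.1 to −0.1, a difference of 0.2 g/dL, moves a patient from 1800 to −1800.
- Among fallers, more dose gives a lower value: 540/(−0.5) = −1080 against 180/(−0.5) = −360.

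Reading the denominator as an absolute change does not help. A fall of 1 g/dL would then score the same as a rise of 1 g/dL.

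**Step 2: how many patients.** Assumption: ΔHb is normal with mean 1.0–1.5 and SD 1.0–1.3 g/dL.
- Fewest non-risers (mean 1.5, SD 1.0): P(ΔHb ≤ 0) = Φ(−1.5/1.0) = 6.7%. With Hb reported to 0.1 g/dL it is Φ((0.05 − 1.5)/1.0) = 7.4%.
- Most non-risers (mean 1.0, SD 1.3): Φ(−1.0/1.3) = 22%. With rounding it is Φ((0.05 − 1.0)/1.3) = 23%.

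That is about 7–23%. Applied to 2,000 patients it would be roughly 140 to 460 (0.07 × 2,000 and 0.23 × 2,000). The efficacy analysis set will be smaller, so these counts are upper figures for each percentage.

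**Step 3: effect on the AUC.** Simulation of 400,000 patients per scenario, with ΔHb rounded to 0.1, dose log-normal and higher in poor responders, zero changes dropped, and event log-odds linear in ΔHb. A binary-event AUC stands in for the time-dependent one.

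| Index | log-odds 0.4 per SD | log-odds 0.7 per SD |
|---|---|---|
| ΔHb alone | 0.61 | 0.68 |
| ERI-2B as written, all scenarios | 0.46–0.57 across both columns | (same range) |
| ERI-2B as written, mean 1.5, SD 1.0 only | 0.54–0.57 across both columns | (same range) |
| ΔHb ÷ dose | 0.60–0.61 | 0.67–0.68 |

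A second simulation used different assumptions: dose independent of response, log-odds 0.6 per g/dL, and zero change coded as +infinity.

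| Mean, SD of ΔHb | ΔHb ≤ 0 | Fallers in lowest ERI-2B quartile | AUC ERI-2B | AUC ΔHb |
|---|---|---|---|---|
| 1.5, 1.0 | 7.4% | 24% | 0.551 | 0.659 |
| 1.5, 1.2 | 11.4% | 39% | 0.528 | 0.687 |
| 1.0, 1.0 | 17.2% | 58% | 0.495 | 0.660 |
| 1.0, 1.2 | 21.5% | 75% | 0.466 | 0.687 |

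The lowest quartile is the one a reader would take as the best responders.

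**Step 4: a direct dose effect.** Section 2 leaves open whether high ESA dose is itself harmful. Adding a dose effect of the same size raises the ERI-2B AUC to 0.59–0.64 at mean 1.5, SD 1.0, and to 0.55–0.58 at mean 1.5, SD 1.2. It stays at 0.44–0.53 when the mean is 1.0.

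**The case against.** The best defence has four parts.

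- **The indices are exploratory.** They are candidates in a study with no hypothesis to verify (13.3), and 12.3 allows new indices if none is associated with events. That bears on severity. It does not remove the problem: the search for new indices starts only if no candidate succeeds, so a success for ERI-1 or plain Hb change would leave the ERI-2 failure unexamined.
- **The SAP may hold a derivation rule.** It is not shown. But the protocol itself fixes both the formula and its use in the sweep. A rule that simply dropped non-risers would remove the patients of interest.
- **Other routes to the answer exist.** Plain Hb change is itself a candidate and orders non-risers correctly. The proportional hazards model enters week-12 Hb and dose as separate covariates. This stands and limits the damage to the two ratio indices.
- **The size depends on assumptions.** This also stands: with few non-risers, or with a direct dose effect, the AUC is reduced by less.

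A reader might infer more than the protocol supports:
- That patients with no Hb change also rank as best responders. They do not: their value is undefined, and they either drop out or, if coded as +infinity, rank as worst.
- That the AUC must fall to about 0.5. At mean 1.5 and SD 1.0 it is 0.54–0.57.
- That all dose-adjusted indices would be lost. ERI-1A and ERI-1B adjust for dose and are unaffected.
- That every cut-off would be meaningless. Section 13.3.1 sets one only conditionally, and the ordering among risers is intact.
- That the early-week versions will certainly be affected. Weeks 10 to 2 are reached only if the 12-week index predicts well.

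**Conclusion.** The misordering is certain, because it follows from the formula and the sweep. ERI-2A and ERI-2B place every patient whose Hb fell on the good-response side of every patient whose Hb rose, and have no value at zero change.

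The numerical size is conditional. It rests on an assumed normal Hb change with mean 1.0–1.5 and SD 1.0–1.3 g/dL and on event risk driven by Hb change. Under those assumptions the indices misplace or leave undefined about 7–23% of patients, and they lose from a few hundredths to more than 0.2 of AUC against the Hb change alone.

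The practical risk is that the AUC comparison wrongly rejects the cumulative-dose indices. This is a should-fix point: the indices are exploratory, and dose, Hb and weight are all collected, so they can be recomputed at any time before analysis.

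**What to change.** In section 12.3, redefine ERI-2A as Hb change ÷ (total dose ÷ weight) and ERI-2B as Hb change ÷ total dose, and state that low values mean poor response. Use the same form at every other week at which the index is built. Because total dose is above zero, the index is always defined, is continuous at zero change and keeps every non-riser below every riser.

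Two downsides should be stated:
- The reciprocal scale is less familiar to clinicians.
- Among patients whose Hb fell, a larger dose still moves the value towards zero: −0.5/540 = −0.0009 against −0.5/180 = −0.0028. Either declare this limit, or add a sensitivity analysis that ranks all non-risers together as the poorest group.

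The cost is wording in 12.3 and the derivation code. No new data are needed.

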### 5.1 Selection criteria

- 1) Patients who are scheduled to start treatment with darbepoetin alfa within eight weeks after registration and who have not received ESA within 12 weeks prior to registration
- 2) Patients with an eGFR less than 60 mL/min/1.73 m^2 at the latest inspection within eight weeks prior to registration
- 3) Patients with an Hb concentration less than 11.0 g/dL at the latest inspection within eight weeks prior to registration
- 4) Patients aged over 20 years at the time of consent acquisition
- 5) Patients who voluntarily provide written consent regarding participation in this research

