#### 8.1.1 Target values of renal anemia treatment

Refer to the latest information, such as the guidelines of academic societies, etc., for the target Hb concentration in ESA therapy.

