**Table Target Hb concentrations of each guideline and the Hb concentration at the start of treatment**

| Guideline                 | Target Hb concentration                                               | Hb concentration at the start of treatment |
|---------------------------|-----------------------------------------------------------------------|--------------------------------------------|
| 2008 Japanese Society for | Over 11 g/dL. Consider dose reduction / suspension if over 13 g/dL*1. | Less than 11 g/dL                          |

| Dialysis Therapy                  |                                                                         |                                 |
|-----------------------------------|-------------------------------------------------------------------------|---------------------------------|
| 2012
CKD clinical
guideline | 10-12 g/dL. Take measures not to exceed 12 g/dL. Do not exceed 13 g/dL. | Less than 10 g/dL               |
| 2012
KDIGO guideline           | 10-11.5 g/dL *2 . Do not exceed 13 g/dL.                     | Less than 10 g/dL *3 |

\* 1 However, consider dose reduction/suspension for patients already with or who have complications of serious CVD or those with medical needs when the Hb concentration exceeds 12 g/dL.

\* 2 Quality of life (QoL) may improve in certain patient groups even when the Hb concentration exceeds 11.5 g/dL and makes the risk acceptable, so it is thought that treatment according to each individual patient is needed.

\* 3 QoL may improve in certain patient groups at even higher Hb concentrations, and ESA therapy may start at a stage of >10 g/dL, so treatment according to each individual patient is valid.

(Reference: "Evidence-based CKD practice guideline 2013")

(refer to the package insert, 2008 edition of the "Guidelines for the treatment of renal anemia in patients with chronic kidney disease" by the Japanese Society for Dialysis Therapy)

The package insert (excerpt) is shown below.

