#### 【Dose adjustment】

The dose should be adjusted with reference to Table 8.2-1 in cases where dose adjustments are necessary, such as when appropriate increases in the Hb concentration or hematocrit value are not observed in the initial administration period, or when the Hb concentration or hematocrit

value deviated from the target range for two consecutive weeks during the maintenance administration period. When increasing doses, do so one step at a time as a general rule.

The table below shows the dose adjustment table for subcutaneous administration. The latest package insert for intravenous injections was followed.

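### The Hb-change index is evaluated without adjustment for start-of-treatment Hb, so in a cohort treated toward a target it partly reflects how anemic patients were at the start

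*Protocol*

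**What the plan says.** - **Index.** Section 12.3 lists five candidates. The fifth is "Change in Hb concentration (changes in Hb concentration up to 12 weeks", computed as week-12 Hb minus "prior Hb concentration (g/dL". It has no dose term, and the time point of the prior value is not defined. An amount of change, evidently the same difference, is also the denominator of ERI-2A and ERI-2B.
- **Entry.** Section 5.1 admits "Patients with an Hb concentration less than 11.0 g/dL at the latest inspection within eight weeks prior to registration". There is no lower limit.
- **Target.** Section 8.1.1 leaves the target to guidelines: "Refer to the latest information, such as the guidelines of academic societies, etc., for the target Hb concentration in ESA therapy". The table in 8.1.2 shows three, one of which is "10-12 g/dL. Take measures not to exceed 12 g/dL. Do not exceed 13 g/dL"; the others are over 11 and 10 to 11.5 g/dL. The package-insert excerpt adjusts the dose when the rise is inadequate or Hb is off target: "When increasing doses, do so one step at a time as a general rule".
- **Evaluation.** Section 13.3.1 first fits a proportional hazards model whose covariates include "eGFR, serum albumin, hemoglobin concentration, high-sensitive CRP, NT-pro BNP" and other markers, all at 12 weeks. In a separate next step it moves each index through its cut-offs, compares time-dependent ROC curves and draws two-group Kaplan-Meier plots. No adjustment is stated for that step.
- **Availability.** Section 13.2.2 removes from the efficacy set patients for whom "Hb concentration measurements are not obtained at the start of treatment and at 12 weeks". Read as requiring both values, this makes start-of-treatment Hb available for everyone analyzed.

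**The concern.** When treatment aims at a range, the intended rise depends on the starting point. Two invented patients show it. One goes from 10.7 to 11.3 g/dL, a change of +0.6, and ends inside every range in the 8.1.2 table. The other goes from 7.5 to 9.0, a change of +1.5, and ends below all of them. Raw change ranks the second as the better responder. Measurement error in a single starting value pushes the same way, because a chance low start inflates the later rise.

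The study exists to find a response index that predicts renal and cardiovascular events and, by section 2, to propose cut-off values for practice. If low starting Hb itself carries risk, patients with large rises are partly those at higher risk. The association between poor response and events is then diluted, and a useful candidate could be ranked too low or given a misplaced cut-off.

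**Working it through.** **1. Inputs.** The protocol gives no SD of Hb at either time and no correlation between them, so there is no plan figure to reproduce on this point. The only plan figure used is the event rate in 13.1. It is consistent with the plan's own count: 2,000 × 0.131 × 2 = 524 events, and 524 ± 1.96 × √524 = 479.1 to 568.9, within one event of the stated 480 to 568. Everything about Hb below is an assumption, shown over a range.

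**2. How far change depends on starting Hb.** Let s0 and s12 be the SDs at start and week 12, and r their correlation. Then

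corr(change, start) = (r·s12 − s0) / √(s0² + s12² − 2·r·s0·s12).

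For example, with s12/s0 = 0.75 and r = 0: −1/√(1 + 0.5625) = −0.80, which squares to 64%. Share of the variance of the change explained by starting Hb:

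| s12/s0 | r = 0 | r = 0.2 | r = 0.4 | r = 0.6 | r = 0.8 |
|---|---|---|---|---|---|
| 0.75 | 64% | 57% | 51% | 46% | 44% |
| 1.0 | 50% | 40% | 30% | 20% | 10% |
| 1.25 | 39% | 27% | 16% | 6% | 0% |
| 1.5 | 31% | 18% | 8% | 1% | 5% |

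The correlation is negative except in the last column at 1.25 (0.00) and 1.5 (+0.22). The share reaches half only when week-12 Hb varies less than starting Hb, or is unrelated to it.

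**3. With entry cut off at 11.0.** Simulated starting Hb below 11 (mean 9.7, SD 0.8); week-12 Hb = 11 + slope × (start − mean) + error.

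| Slope, error SD | Spearman (change, start) | Mean start: lowest change quartile vs rest |
|---|---|---|
| 0, 0.8 | −0.68 | 10.35 vs 9.50 |
| 0.5, 1.0 | −0.35 | 10.06 vs 9.60 |
| 1, 1.0 | about 0 | 9.71 vs 9.71 |

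**4. What it may cost in prediction.** Simulation of 400,000 patients per scenario. Assumptions: start Hb about 9.9, SD 0.9, truncated below 11; week-12 Hb = start + k(11.3 − start) + 0.7 × responsiveness + noise, with k = 0.3, 0.5, 0.7 and measurement SD 0.3; responsiveness independent of starting Hb, with log HR −0.3 per SD; 13.1 events per 100 patient-years over 84 weeks (1.61 years). The 11.3 is a simulation constant only. AUC is the simple rank AUC for an event by 84 weeks; adjusted means the residual of change on starting Hb.

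| Log HR per g/dL of starting Hb | AUC, raw change | AUC, adjusted |
|---|---|---|
| 0 | 0.568–0.578 | 0.582–0.585 |
| −0.25 | 0.538–0.564 | 0.587–0.589 |
| −0.5 | 0.501–0.547 | 0.588–0.591 |

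Change correlates −0.34 to −0.60 with starting Hb, i.e. 0.34² to 0.60² = 12 to 36% of variance. The true lowest response quartile is recovered to 63–71% by raw change and 76–79% after adjustment. Without any pull toward a target, the AUC gain shrinks to about 0.001–0.011.

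**5. Which Hb to pair with the change.** Since Hb12 = Hb0 + change, a·change + b·Hb12 = (a + b)·change + b·Hb0. With week-12 Hb held fixed, change is starting Hb with its sign reversed (partial correlation exactly −1). The two pairings give identical predictions; only the meaning of the coefficient of change differs.

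**The case against.** The index does subtract a starting value, so it cannot be said to ignore it. Under the assumptions of step 4, raw change correlates 0.73 to 0.84 with true responsiveness, more strongly than with starting Hb. A reader might infer that the index ranks patients mainly by how anemic they started; the documents do not support that, because they give no Hb SDs or correlation and the share is below half over most of the assumed range.

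A reader might also infer that the plan's own model would reverse the sign of Hb change, making a good rise look harmful. That needs Hb change and week-12 Hb in one regression. Section 13.3.1 does not specify this: no response index is in its covariate list, and the indices are assessed in a separate step. If the two were combined, step 5 shows that predictions would not change.

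Nor is baseline adjustment ruled out. Section 13.3.1 lets covariates be added and Hb at other time points up to week 24 replace week 12. Hb change is one of five exploratory candidates, ERI-1A and ERI-1B bring in dose and achieved Hb, and the background section cites a precedent based on the rate of Hb change. Dosing is recommended rather than imposed, which may weaken the pull toward a target.

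All of this limits the point without removing it. The index formula, the Hb covariate and the ROC comparison are fixed in the protocol. The open covariate clause permits starting Hb but does not commit to it, and it does not reach the ROC, cut-off and Kaplan-Meier steps, which use the raw index.

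**Conclusion.** The point holds in a limited form. Hb change is evaluated as a raw difference with no stated adjustment for start-of-treatment Hb, in a cohort with no lower Hb limit at entry and dosing recommended toward a target. It therefore partly reflects starting Hb: 0 to 64% of its variance over the assumed SD ratios and correlations, and 12 to 36% in the prognostic simulation. There, when low starting Hb carries risk, the raw AUC is 0.501–0.564 against 0.587–0.591 after adjustment; when it carries none, adjustment still did not lower the AUC. These AUCs rest on assumed hazard ratios, assumed closure of the gap to target, and responsiveness independent of starting Hb, none of which the protocol supplies. They show that dilution is possible, not how large it will be in this cohort.

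**What to change.** 1. In 13.3.1, add start-of-treatment Hb to the covariate list.
2. In 13.3.1, evaluate the prognostic value of Hb change, in both the proportional hazards model and the time-dependent ROC, with start-of-treatment Hb included or stratified by it. Report this alongside the raw index and its simple cut-off, not in place of them, because a residual alone gives no cut-off that carries over easily to other cohorts.
3. If Hb change enters a regression, pair it with start-of-treatment Hb rather than week-12 Hb, so that its coefficient reads as response. All three cannot be entered together, because any two determine the third.
4. In 12.3, state that prior Hb is the start-of-treatment value, not the registration value used for eligibility.

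The cost is a change of wording and a little more analysis on data already required. An adjusted cut-off has to be read at a given starting Hb.

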### 8.3.2 Treatment where concomitant use is prohibited

The administration of drugs of the same type or with the same efficacy as darbepoetin alfa (e.g., epoetin beta pegol, epoetin alfa, epoetin beta) is prohibited during the observation period.

If prohibited concomitant use is applied during the observation period, the reason is recorded in the case report form, and research participation is continued.

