|-----|-------------------------------------------------------------|-----------------------------------------------------------------------------------------------------------------------------------------------------------------------------------------------------------------------------------------------------------------------|---------------------------------------------------------------------------------------------------------------------------------------------------------------------------|--------------------------------------------------------------------------------------------------------------------------------------------------------------------------------------------------------------------------------------------------------------------------------------------------------------------------------------------------------------------------------------------------------------------------------|
|     |                                                             | concomitant use is prohibited                                                                                                                                                                                                                                         | name
Reason for use                                                                                                                                                    | beta
[Written accordingly]                                                                                                                                                                                                                                                                                                                                                                                                  |

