| 7   | Urinalysis (start, 12, 48, 96 weeks)                        | Urine protein (mg/dL), urinary Cr (mg/dL), PCR (protein creatinine ratio (g/Cr): automatically calculated)                                                                                                                                                            |                                                                                                                                                                           |                                                                                                                                                                                                                                                                                                                                                                                                                                |
| 8   | Blood transfusion                                           | Blood transfusion date                                                                                                                                                                                                                                                | yyyy/mm/dd                                                                                                                                                                |                                                                                                                                                                                                                                                                                                                                                                                                                                |

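### The ERI formulas score any rise in Hb as response to darbepoetin, including a rise produced by transfusion or another ESA before the index Hb

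*Protocol*

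**What the plan says.** Section 12.3 defines five week-12 indices. Hb change is "Hb concentration at 12 weeks (g/dL" minus the prior Hb. ERI-1A and 1B take as numerator "DA administered dose 12 weeks after the start of treatment" and divide it by the week-12 Hb, with weight added in 1A. ERI-2A and 2B take "Total DA administered dose up to 12 weeks after the start of treatment" and divide it by the Hb change, with weight added in 2A. Similar indices are to be built at weeks 16 and 24. No formula carries a condition about transfusion or other ESAs.

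Section 8.3.2 says that giving another ESA "is prohibited during the observation period", but it foresees that this will happen: "If prohibited concomitant use is applied during the observation period, the reason is recorded in the case report form, and research participation is continued".

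Section 10.1.3 collects "Blood transfusion date" and the amount transfused. For a prohibited ESA it lists the drug name and "Reason for use", with no field for dose or date.

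Section 13.2.2 removes patients who were ineligible, stopped darbepoetin within 12 weeks, have no darbepoetin record, or lack the Hb values. Transfusion and other-ESA use are not among the exclusions. The compliance set in 13.2.3 depends only on section 8.1.2. Section 13.3.1 names neither event as a covariate or stratification factor.

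**The concern.** The study's main product is an index of low ESA response, with a cut-off, that predicts renal and CVD events. That requires the Hb term to reflect what darbepoetin did. A transfusion raises Hb with no ESA response. Another ESA raises Hb while adding nothing to the darbepoetin numerator, and can lower that numerator if it replaces doses. Transfusion is also most likely in patients whose Hb stays low on treatment, which is the group the index is meant to find. As written, the formulas give these patients a value that does not measure their response, and that value enters the ROC and cut-off analysis with the same standing as any other.

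**Working it through.** The protocol states no figure on this point, so the check puts worked patients through the section 12.3 formulas. All patient values below are assumptions, with Hb in g/dL.

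**Reference responder.** Hb 9.5 to 11.0, six doses of 30 µg (180 µg in total), 30 µg at week 12.
- Hb change = 11.0 − 9.5 = 1.5
- ERI-2B = 180 / 1.5 = 120
- ERI-1B = 30 / 11.0 = 2.7

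**Poor responder, not transfused.** Hb 9.5 to 9.7, 360 µg in total, 120 µg at week 12.
- Hb change = 0.2
- ERI-2B = 360 / 0.2 = 1,800
- ERI-1B = 120 / 9.7 = 12.4

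**Same poor responder, transfused before the week-12 Hb.**

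| Transfusion rise | Hb change | ERI-2B | ERI-1B |
|---|---|---|---|
| 0.5 | 0.7 | 360 / 0.7 = 514 | 120 / 10.2 = 11.8 |
| 1.0 | 1.2 | 360 / 1.2 = 300 | 120 / 10.7 = 11.2 |
| 1.5 | 1.7 | 360 / 1.7 = 212 | 120 / 11.2 = 10.7 |
| 2.0 | 2.2 | 360 / 2.2 = 164 | 120 / 11.7 = 10.3 |

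At a rise of 1.5 the Hb change exceeds the responder's 1.5. ERI-2B falls by most of its value but stays above 120. ERI-1B hardly moves and remains far above 2.7, because dose dominates it. The A versions divide by weight as well and behave in the same way.

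**Direction for ERI-2.** Take 360 µg and a true change of −0.5: ERI-2B = 360 / (−0.5) = −720. After a 1 g/dL rise the change is +0.5 and ERI-2B = 360 / 0.5 = +720. Section 13.3.1 moves the cut-off from the lowest index value to the highest, so −720 lies at the responder end and +720 on the low-response side. For this patient transfusion shifts ERI-2 the opposite way from the patient above.

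**Another ESA in place of most darbepoetin.** Same poor responder, but 60 µg of darbepoetin in total and 30 µg at week 12.

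| Other-ESA effect | Hb change | ERI-2B | ERI-1B |
|---|---|---|---|
| 0.5 | 0.7 | 60 / 0.7 = 86 | 30 / 10.2 = 2.9 |
| 1.0 | 1.2 | 60 / 1.2 = 50 | 30 / 10.7 = 2.8 |
| 1.5 | 1.7 | 60 / 1.7 = 35 | 30 / 11.2 = 2.7 |

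ERI-2B now looks better than the responder's 120, and ERI-1B is about equal to the responder's 2.7.

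**Bound on reclassification for Hb change.** The lowest quartile holds 25% of patients. If 2% are transfused, all inside it, at most 2/25 = 8% of the quartile can leave it; if 5%, at most 5/25 = 20%. Both the frequencies and their placement are assumptions.

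**The case against.** The strongest reply is that this belongs in the SAP. Section 13.3 refers unrecorded analyses there, 13.2 allows decisions on individual patients before the data are fixed, and the covariate list in 13.3.1 is open. The indices are called candidates and no hypothesis is tested. Part of this stands: a rule may exist in the SAP, and nothing here invalidates a confirmatory test. But the formulas and the exclusion list are written in the protocol, so an SAP rule that altered them would depart from it. The case-by-case review states no criterion for transfusion or other-ESA use.

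Several stronger readings are tempting, and the documents do not support them:
- A reader might infer that the error always moves poor responders to the responder side. The −720 to +720 example shows that this fails for ERI-2 when Hb has truly fallen.
- A reader might infer that transfusion damages all five indices alike. ERI-1B moves only from 12.4 to 11.2 for a 1 g/dL rise.
- A reader might take 8–20% as an estimate. It is an upper bound for Hb change alone and follows almost entirely from its assumptions.
- A reader might infer a known shift in the cut-off or a weakened association with events. Neither can be calculated from the protocol.

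The other-ESA part is also limited. A patient who switched completely before week 12 is probably already removed for stopping darbepoetin, so at week 12 the issue is added or temporary use. That exclusion does not reach a switch after week 12, which could still affect the week-16 and week-24 indices.

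**Conclusion.** The concern holds in this limited form. Followed as written, section 12.3 counts a rise in Hb from transfusion or another ESA as response to darbepoetin, and sections 13.2.2, 13.2.3 and 13.3.1 neither remove nor adjust for it. For an individual patient the distortion can be large on Hb change and ERI-2A/2B, and modest on ERI-1A/1B when the cause is transfusion. Other-ESA use alongside or in place of some darbepoetin can distort all five. The worked sizes rest on assumed doses and Hb effects of 0.5–2.0 g/dL. How much the cut-offs and AUC would change is unknown, because the protocol gives no frequency for either event. The point merits a correction because it touches the study's main product and the correction is cheap.

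**What to change.** In 12.3 and 13.2.2, flag every patient with a transfusion or other-ESA use between treatment start and the index Hb, separately for weeks 12, 16 and 24. Transfusion can be placed by its recorded date. Other-ESA use can be placed only to the survey interval, and its dose cannot be added to the index because no dose field is listed.

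State that the index Hb of flagged patients is not treated as evidence of response. Repeat the time-dependent ROC, cut-off and Cox analyses without them, and report whether the cut-off and AUC change.

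Do not recompute the index from the last Hb and cumulative dose before the event. A shortened dose period makes ERI-2 values non-comparable between patients: with an assumed 60 µg given before an early transfusion and a change of 0.2, it gives 60 / 0.2 = 300, the same value as the distorted one. Classing transfused patients as low response may be added only as a further sensitivity analysis of the dichotomised comparison.

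The cost is a few lines of text, a little extra analysis and a small loss of patients in the repeated analyses. No new data collection is needed.
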